### Study analysis

#### Volumetric analysis

Volume resorption will be evaluated by comparing the cone-beam computed tomography tests performed after (T2) the graft placement and eight months later (T3) with the software Horus Project®. In addition, from the CBCT T2 test, an analysis regarding the adaptation of the bone graft to the residual bone will be performed in both groups.

#### Biopsies analyses

##### Histological analysis

The obtained biopsies will be immediately stored in paraformaldehyde 4% for 48h and after immersed in 70° alcohol solution for the micro-tomographic test. Then, the biopsies will be washed with running water for subsequent immersion in EDTA solution, which will be changed three times a week for 50 days. After evaluating the correct decalcification of the biopsies, the dehydration process will be carried out. Dehydration will be done in increasing alcohol baths (70°, 90°, absolute alcohol), allowing the piece to be finally cleared in xylene for 3 h and embedded in paraffin.

The mini-implant biopsies will be washed with running water for 6 hours and then dehydrated in a growing series of ethanol (60–100%) and infiltrated and polymerized in light-curing resin (Technovit 7200 VLC, Kulzer Heraeus GmbH & CO, Wehrheim, Germany).

##### Micro-tomographic analysis

Before starting the process for inclusion in paraffin, the biopsies will be scanned by a microtomography (Skyscan®, Aatselaar, Belgium. Camera Pixel: 12.45; X-ray tube power: 65 kVP, X-ray intensity: 385 μA, integration time: 300 ms, filter: Al-1 mm and voxel size: 18 μm3c). Then, the images will be reconstructed, spatially repositioned, and analyzed by specific software (NRecon, Data Viewer, CTAnalyser, Aatselaar, Belgium). The threshold used in the analysis will be 25–90 shades of gray, and the values of mineralized tissue volumes will be obtained as a percentage. A trained examiner blinded to the experimental groups will perform this analysis.

##### Histomorphometric analysis

The paraffin blocks will be cut in serial cuts with 4μm thick along their entire length. To obtain the histological blades, the pattern of selecting the center cut of the block will be followed. Blades will be stained with hematoxylin and eosin (HE, Merck & Co. Inc., New Jersey, USA). Blades images will be captured and scanned using an optical microscope with fourfold magnification objectives and 5-fold magnification eyepieces (Diastar - Leica Reichert & Jung products, Germany), with a digital camera (DFC-300-FX, Leica Microsystems, Germany) with 1.3-megapixel resolution coupled to this microscope and connected to a microcomputer with a digitalized image analyzer software Image J 1,45 (Wayne Rasband National Institutes of Health, USA). The following parameters will be evaluated: newly formed bone percentage, soft tissue percentage, and residual bone graft percentage. Measurements will be performed by a single calibrated examiner blinded to experimental groups.

The mini-implant blocks with bone tissue will be cut at a central point using a cut and wear system (Exakt Apparatebeau, Hamburgo, Germany). The sections will be approximately 45 μm thick, stained with Stevenel’s blue associated with acid fuchsin, and analyzed under an optical microscope (DIASTAR – Leica Reichert & Jung products, Wetzlar, Germany) at × 100 magnification. Histomorphometric evaluations will be performed with the image analysis software (Image J, San Rafael, CA, USA). In addition, the percentages of bone-implant contact (%BIC) and the bone area between turns (%BBT) will be evaluated separately in the region between bone tissue and the center of the mini-implant. A blind and trained examiner will perform these analyses.

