### Outcomes {12}

#### Primary endpoints

Evaluate the gain of increase/maintenance of the volume of the bone graft area and the quality of the newly formed bone tissue after eight months of the postoperative between the synthetic graft in a personalized block with the autogenous bone graft.

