##### Immunohistochemical analysis

Histological sections from the same paraffin blocks used for the histomorphometric analysis will be mounted on blades with an appropriate glass surface (Fisher Superfrost Plus; Thermo Fisher Scientific - Waltham MA, USA). The immunohistochemical reaction will be performed using the indirect immunoperoxidase technique with an amplifier. Therefore, 3% hydrogen peroxide will be used (Merck Laboratories, Kenilworth, Nova Jersey, USA) to inhibit endogenous peroxidase. Antigen recovery will be performed by immersing the slides in citrate phosphate buffer, pH = 6, kept in a steamer (moist heat) for 20 min. Blocks of nonspecific reactions will be performed with bovine albumin (Sigma, San Luis, Missouri, USA) and skim milk. The primary antibodies against osteocalcin, alkaline phosphatase, VEGF, and BMP2 (Santa Cruz Biotechnology, Dallas, TX, EUA) are bone metabolism markers. BMP2 is one of the main proteins related to bone neoformation and development, while alkaline phosphatase and osteocalcin allow the evaluation of collagen matrix production and bone mineralization. Vascular endothelial growth factor (VEGF) enables the assessment of local angiogenesis. As a secondary antibody, the biotinylated anti-goat antibody produced in rabbits will be used (Pierce Biotechnology, Waltham, Massachusetts, USA); the amplifier will be Avidin and Biotin (Vector Laboratories, Burlingame, California, USA), and diaminobenzidine (DakoCytomation, Carpinteria, California, USA) will be used as the chromogen. At the end of the revelation by diaminobenzidine, the counterstaining of the histological sections will be performed with Harris hematoxylin. The sections will be analyzed under an optical microscope (LeicaR® DMLB, Heerbrugg, Switzerland) as well as the expression of proteins, coupled to an image capture camera (Leica^®^ DFC 300FX, Leica microsystems, Heerbrugg, Switzerland) and connected to a microcomputer with scanned image analyzer software (Leica Camera Software Box^®^, Leica Imaging Manager -IM50 Demo Software).

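### Each biopsy block is sectioned throughout, but only the central section is described as read for the three tissue percentages, an avoidable loss of precision

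*Protocol article*

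**What the plan says.** The protocol's Histomorphometric analysis section states that "The paraffin blocks will be cut in serial cuts with 4μm thick along their entire length". For the slides that are stained and measured, "the pattern of selecting the center cut of the block will be followed". The parameters read are "newly formed bone percentage, soft tissue percentage, and residual bone graft percentage", and "Measurements will be performed by a single calibrated examiner blinded to experimental groups". No second level, number of sections or averaging is described.

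Under Secondary endpoints, these three percentages are the means of assessing bone neoformation. Primary endpoints also includes "the quality of the newly formed bone tissue after eight months of the postoperative". Dental implants installation and biopsy explains that the biopsy is oriented so that it takes in both residual and newly formed bone.

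Two other analyses use the same specimens. In Micro-tomographic analysis, the biopsy is scanned before embedding and "the values of mineralized tissue volumes will be obtained as a percentage". In Immunohistochemical analysis, "Histological sections from the same paraffin blocks used for the histomorphometric analysis will be mounted on blades".

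**The concern.** An area fraction measured on one thin plane estimates the fraction in the whole biopsy, and its error depends on how much the tissue changes from plane to plane. Here the specimen is mixed by design, since it contains residual bone, new bone and possibly remaining graft, and the test material is described as porous. Some variation between sections is therefore to be expected. With one plane per graft, all of that variation passes into the graft's value and from there into the comparison between grafts.

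The loss is avoidable because the block is already cut along its whole length; further levels need only be stained and read. It matters because histomorphometry is the only described measure that separates new bone, soft tissue and residual graft. In addition, the 20 participants were chosen for a CBCT volume outcome, so nothing in the plan shows how precise the histological comparison will be.

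**Working it through.** **1. The plan's own figure.** Sample size {14} uses a difference of 11.90 and an SD of 12.09 in percentage volume reduction, with power 0.80 and alpha 0.05. A two-sided two-sample t-test (noncentral t) with these inputs needs 18 per group (power 0.818); at 20 per group the power is 0.858. The stated 20 is thus close to reproduced. It rests on CBCT volume and does not depend on how many histological sections are read.

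**2. Model for the percentages.** Let V be the variance between biopsies and W the variance between sections within a biopsy. A graft's value from the mean of k sections has variance V + W/k. With L = W/(V + W), the share of single-section variance that comes from section-to-section variation, the variance relative to one section is

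(1 − L) + L/k.

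The document gives neither V nor W, so L is an assumption and a range is shown. The formula treats the k sections as spaced widely enough to vary independently around the biopsy's mean.

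**3. Three sections, k = 3.** The equivalent number of participants is 20 divided by the ratio.

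| Assumed L | Calculation | Variance ratio | Reduction | Equivalent n |
|---|---|---|---|---|
| 0.1 | 0.9 + 0.1/3 | 0.933 | 7% | 21.4 |
| 0.2 | 0.8 + 0.2/3 | 0.867 | 13% | 23.1 |
| 0.3 | 0.7 + 0.3/3 | 0.800 | 20% | 25.0 |
| 0.5 | 0.5 + 0.5/3 | 0.667 | 33% | 30.0 |

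With five sections the ratios are 0.920, 0.840, 0.760 and 0.600, so most of the gain comes from the first three.

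**4. What this means for power.** Suppose one section per graft gave exactly 80% power at 20 per group in the unpaired t-test named under Statistical methods {20a}. The standardised difference is then 0.909. Dividing it by the square root of each ratio in step 3 gives power of about 83%, 85%, 88% and 93% with three sections. The 80% starting point is illustrative; the protocol states no power for histology.

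**5. Workload.** One section per graft: 20 × 2 × 1 = 40. Three sections per graft: 20 × 2 × 3 = 120, that is, 80 more.

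**The case against.** The strongest defence is that the rule is explicit, fixed in advance, the same for both grafts, and applied by one calibrated examiner who does not know the group. It prevents anyone from picking a favourable section. That stands: a reader might infer that the central section biases the comparison, but nothing in the document shows that it favours either graft.

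Three further inferences are tempting but unsupported:

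- **A regular strut or lattice structure, and hence more variation in the test graft.** The protocol calls the device porous and lists control of porosity and interconnected pores as general advantages of additive manufacturing. It describes no lattice or periodicity, says that the material is resorbed and replaced, and gives no basis for expecting more section-to-section variation on one side.
- **The remaining sections go unused.** Immunohistochemistry takes sections from the same blocks. The accurate statement is that no other section is described as read for these three percentages.
- **These percentages are the only evidence on bone quality.** Micro-CT, four immunohistochemical markers and, where mini-implants are placed, bone-implant contact and bone area between turns also contribute. Micro-CT does not depend on a single plane, but it reports only total mineralised volume and cannot separate new bone from residual graft.

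Two cautions also stand. If L is small, the gain is small: at L = 0.1, power moves only from 80% to about 83%. And the cutting direction is not stated. If cuts run across the biopsy, evenly spaced levels could fall in native bone, and a plain mean would mix it into the result. The fix must allow for this.

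**Conclusion.** The point holds as a loss of precision that could be avoided cheaply. One plane per graft is the only sampling described for the three percentages, and for any L above zero the mean of several suitably spaced sections has lower variance. The direction is certain under that model, but the size is not: the reduction of 7% to 33% with three sections rests on an assumed L of 0.1 to 0.5 and on sections varying independently within the biopsy. Sections that are too close together, or that carry similar information, would gain less.

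The reach is limited. The sample size of 20 and the volumetric part of the primary endpoint are untouched. What is affected is one secondary endpoint and, through it, the bone-quality element of the primary endpoint.

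**What to change.** In Histomorphometric analysis, replace the central-section rule with at least three systematically spaced sections per block, at positions fixed before reading. State the cutting direction, and define the positions so that they cover the same grafted region on both sides and follow one rule for both grafts. The same blinded examiner reads all sections, and their mean is the single value for that graft. The graft site within the patient stays the unit of analysis, so that sections are not counted as independent observations.

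The cost is about 80 more hematoxylin-and-eosin sections to stain and read (120 instead of 40). No new biopsy, participant or staff is needed. Enough sections must be reserved for the immunohistochemistry on the same blocks.

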##### Immunohistochemical analysis

Histological sections from the same paraffin blocks used for the histomorphometric analysis will be mounted on blades with an appropriate glass surface (Fisher Superfrost Plus; Thermo Fisher Scientific - Waltham MA, USA). The immunohistochemical reaction will be performed using the indirect immunoperoxidase technique with an amplifier. Therefore, 3% hydrogen peroxide will be used (Merck Laboratories, Kenilworth, Nova Jersey, USA) to inhibit endogenous peroxidase. Antigen recovery will be performed by immersing the slides in citrate phosphate buffer, pH = 6, kept in a steamer (moist heat) for 20 min. Blocks of nonspecific reactions will be performed with bovine albumin (Sigma, San Luis, Missouri, USA) and skim milk. The primary antibodies against osteocalcin, alkaline phosphatase, VEGF, and BMP2 (Santa Cruz Biotechnology, Dallas, TX, EUA) are bone metabolism markers. BMP2 is one of the main proteins related to bone neoformation and development, while alkaline phosphatase and osteocalcin allow the evaluation of collagen matrix production and bone mineralization. Vascular endothelial growth factor (VEGF) enables the assessment of local angiogenesis. As a secondary antibody, the biotinylated anti-goat antibody produced in rabbits will be used (Pierce Biotechnology, Waltham, Massachusetts, USA); the amplifier will be Avidin and Biotin (Vector Laboratories, Burlingame, California, USA), and diaminobenzidine (DakoCytomation, Carpinteria, California, USA) will be used as the chromogen. At the end of the revelation by diaminobenzidine, the counterstaining of the histological sections will be performed with Harris hematoxylin. The sections will be analyzed under an optical microscope (LeicaR® DMLB, Heerbrugg, Switzerland) as well as the expression of proteins, coupled to an image capture camera (Leica^®^ DFC 300FX, Leica microsystems, Heerbrugg, Switzerland) and connected to a microcomputer with scanned image analyzer software (Leica Camera Software Box^®^, Leica Imaging Manager -IM50 Demo Software).

#### Implant stability analysis

The primary and secondary implant stability will be analyzed using the Osstell^®^ device (Osstell AB, Gothenburg, Sweden). This device determines the implant stability by the resonance frequency analysis. The system includes using a SmartPeg fixed to the implant through an integrated screw. The SmartPeg is excited by a magnetic impulse from the measuring probe of the portable instrument, and the implant stability coefficient (ISQ) is calculated from the response signal. Results are displayed on the instrument ranging from 1 to 100. The higher the ISQ number, the greater the stability of the implant.

Stability measurements will be obtained in two directions: buccal-palatal and mesiodistal. Values will be compared within groups about primary and secondary stability. They will also be compared between groups to assess whether there is a difference between implant stability in the test and control groups.

### Participant timeline {13}

**Table Tabb:** 

	Study period				
	Enrollment	Allocation	Post allocation		
Timepoint	− ***T***_**1**_	T0	T1 (intervention)	T2 (8-month follow up)	T3 (14-month follow up)
Patients visits	x				
Eligibility screen	x				
Informed consent	x				
Randomization: split-mouth		x			
**Intervention**					
Tomography (T1, T2, and T3)	x		x	x	
Graft installation			x		
Implant placement and biopsies				x	
Healing caps placement					x
**Assessments**					
Surgery analysis			x		
Implant stability				x	x
Biopsies				x	
Biopsies analyses				x	x
Adverse events			x	x	x

### Sample size {14}

Sample calculations were performed based on tomographic bone formation data from the study, which evaluated the volumetric stability of autogenous and allogeneic corticomedullary block grafts used for volume increase associated with edentulous alveolar ridges [19]. This choice was due to the lack of studies comparing β-tricalcium phosphate blocks and autogenous bone and the similarity of the methodology for evaluating the stability of block grafts. As a result, it was verified that the minimum difference between the means of treatments concerning the percentage of volumetric reduction of the graft was 11.90, with a standard deviation of 12.09. Therefore, considering a study power (1-β) of 0.8 and an *α* power of 0.05, a minimum sample of 20 participants was determined, each of whom will receive two grafts, one synthetic in a personalized block and another in an autogenous block. To maintain the power of the study, the sample size should be maintained, thus if any participant dropout or is discontinued before the analysis of the primary outcome, a new participant will be recruited instead, until complete 20 participants.

### Recruitment {15}

Recruitment will be performed by local radio and social media (Facebook). The advertisement will invite patients who need implant rehabilitation on both sides of the maxilla, and after the patients attend a screening visit, the inclusion criteria will be assessed. Additionally, as the study will be carried out at a public university that serves patients free of charge in various undergraduate and graduate courses, the study will be disseminated to students and professors, allowing them to refer patients with the necessary inclusion criteria to be enrolled in this study.

## Assignment of interventions: allocation

### Sequence generation {16a}

The treatments will be randomized using 20 binary sets (0- control treatment: autogenous graft and 1- test treatment: Plenum^®^ Oss 3D_β_ fit). The sets, 1 to 20, will correspond to each patient according to the enrolment order. The binaries numbers 0 and 1 will be randomized, corresponding to the treatment that will be applied. From left to right, the first number will define the treatment of the right side of the maxilla, and the second number will determine the treatment which will be applied on the left side.

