### Who will take informed consent? {26a}

The consent process will be done jointly by the principal investigator, or a member of his team already assigned to this task and the patient. The application of the term will be in the clinic, and in this consultation, participants will have the opportunity to ask questions, check visits, follow-up time, risks, and benefits of the study. In addition, the participants can take the term with them, to discuss with people they trust, if they wish. If the patient decides to participate in the study, the term must be rubricated by the responsible for the application and the patient, and be signed on the last page, always in two copies, one for the patient and another copy for being kept at the center until the end of the study. Upon completion of the study, the consent form will be stored by the sponsor.

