#### Preparation and installation of the autogenous bone graft and Plenum^®^ Oss 3D_β_ fit

The intra- and extra-oral asepsis will be performed with 0.12% and 2% chlorhexidine digluconate. Next, the local anesthesia will be applied with Articaine 4% 1:100.000 (Nova DFL, Brazil), followed by a linear incision over the alveolar crest and two vertical incisions. Next, the mucoperiosteal flap will be detached, and the autogenous bone graft collection will be started. A linear incision will also be made in the donor site, followed by a mucoperiosteal flap detachment and a mandible branch exposure. Trunk-conical drills and discs mounted in a straight handpiece will be used for osteotomy. After the graft removal, it will incubate in saline solution while the receptor site is prepared. Grooves will be performed in the receptor site to stimulate the vascularization, and the autogenous bone graft will be fixed in the anterior region of the maxilla by fixing screws. On the opposite side of the maxilla (test group), grooves will also be performed, and the 3D printed block will also be fixed by fixing screws. Then, a resorbable polydioxanone membrane, Plenum^®^ Guide (Plenum, Jundiaí, São Paulo, Brazil) will be used over 3 to 4 mm of the bone grafts, and the suture will be performed with Nylon 5.0 (Ethicon^®^, Jonhson & Jonhson, New Brunswick, Nova Jersey, EUA). All surgical procedures will be performed by the same professional.

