### Concealment mechanism {16b}

Randomization of treatments will be performed using the ResearchRandomizer software (https://www.randomizer.org/).

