### Implementation {16c}

The trial sponsor and the Principal investigator team will generate randomization with the allocation sequence.

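### The concealment item names only sequence-generating software, the team that takes consent helps make the sequence, and allocation of replacement patients is not specified

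*Protocol article*

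**What the plan says.** - **Sequence generation {16a}:** "The treatments will be randomized using 20 binary sets". Within a set, "the first number will define the treatment of the right side of the maxilla", and the second number gives the left side. The link to patients is: "The sets, 1 to 20, will correspond to each patient according to the enrolment order".
- **Concealment mechanism {16b}:** apart from a web address, the whole entry is "Randomization of treatments will be performed using the ResearchRandomizer software".
- **Implementation {16c}:** "The trial sponsor and the Principal investigator team will generate randomization with the allocation sequence".
- **Who will take informed consent? {26a}:** "The consent process will be done jointly by the principal investigator, or a member of his team".
- **Trial design {8} and Who will be blinded {17a}:** the trial is open and single-centre, and each patient receives both grafts.
- **Participant timeline {13}:** eligibility, consent and the first tomography stand in the enrolment column. Randomisation stands in the next column, before graft surgery.
- **Sample size {14}:** for anyone lost before the primary analysis, "a new participant will be recruited instead, until complete 20 participants". The section on non-adherence and missing data {20c} repeats the rule, counting until biopsies from 20 participants are in hand. Section {18b} keeps the data already collected from those who leave.

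**The concern.** There are two separate problems.

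**Foreseeable side.** Concealment means that whoever decides on a patient's entry cannot know that patient's assignment. Software that generates a sequence does not do this by itself. Here the enrolling team shares in making the list, and the list is used in order of entry. Someone who knows the next set, and who has seen from the pre-operative scan that the two sides differ, could admit, defer or reorder patients so that one graft more often meets the easier side. The eligibility criteria leave room for this, since some of them (oral hygiene, expectations) are matters of judgement. A systematic difference between the sides given to each graft would enter the within-patient comparison directly.

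**List too short for the plan's own rule.** Twenty is the required number of completers, and it is also the number of sets. The first replacement is the 21st patient to enter, and the article provides no set for that patient.

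**Working it through.** **1. Who makes the list and who enrols**

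| Task | Who, according to the article | Section |
|---|---|---|
| Generate the sequence | Sponsor together with the principal investigator team | {16c} |
| Take consent | Principal investigator or a team member | {26a} |
| Plan the printed block | A trained professional, affiliation not given | Planning and production |
| Operate | One professional, affiliation not given ("All surgical procedures will be performed by the same professional") | Preparation and installation |
| Hold the list and release sets | Not stated | – |

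The documented overlap is between generation and consent. That is enough for an enroller to be able to foresee the next side.

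**2. The plan's figure of 20**

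Inputs from Sample size {14}: difference 11.90, SD 12.09, power 0.80, alpha 0.05 (taken as two-sided, which the article does not state). An unpaired t-test needs 17.22, so 18 per group. With 20 per group the power is about 86%. The stated 20 is therefore close to what its inputs give. It is a number of patients to be completed, with no allowance for loss, because loss is handled by replacement.

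**3. Sets available against sets needed**

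Sets available: 20. The article gives no loss rate, so a range of f is assumed, with losses independent between patients.

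- Expected replacements to reach 20 completers: 20 × f / (1 − f)
- Chance that at least one of the first 20 is lost, so that a 21st set is needed: 1 − (1 − f)^20
- Sets needed on average: 20 / (1 − f), rounded up

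| Assumed f | Expected replacements | Chance a 21st set is needed | Sets needed on average |
|---|---|---|---|
| 5% | 20 × 0.05 / 0.95 = 1.05 | 1 − 0.95^20 = 64% | 22 |
| 10% | 20 × 0.10 / 0.90 = 2.2 | 1 − 0.90^20 = 88% | 23 |
| 15% | 20 × 0.15 / 0.85 = 3.5 | 1 − 0.85^20 = 96% | 24 |
| 20% | 20 × 0.20 / 0.80 = 5.0 | 1 − 0.80^20 = 99% | 25 |

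A list of 30 sets covers 30 − 20 = 10 replacements.

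**4. Could a replacement take over the lost patient's set?**

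The article does not say so. It would depart from the enrolment-order rule, and the set would already be known before the new patient entered. The lost patient's data also stay in the analysis under {18b}, so that set is already in use.

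**The case against.** The strongest reply is that the timeline already places consent, eligibility and the first scan before randomisation, which is much of what one would ask for. This is true and should be credited. It fixes the order of steps, but it does not hide a list that the enrolling team helped to make beforehand.

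It can also be said that the sponsor shares in generation, that using sets in order of entry is normal practice, and that custody of the list may be described in the full protocol. All three are fair. The finding rests on what the article does state: its concealment entry names only a generation tool, and generation is shared with the team that takes consent.

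Four stronger readings are tempting, and the documents do not support them:

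- *The generating team also plans and operates.* The sections on planning and surgery do not place those professionals in or outside the principal investigator team.
- *The enrollers know every next allocation for certain.* The article does not say who sees the list or when. What follows from it is that they can know.
- *Replacements are not randomised.* The article is silent, and the same software could produce further sets. The accurate statement is that their allocation is not specified.
- *This is the main route to bias in the trial.* Nothing in the article ranks it so. With both grafts in each patient, foreknowledge acts only through the choice and order of patients with unequal sides, which is narrower than in a parallel-group trial.

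**Conclusion.** The concern holds in a limited form, and the plan should be changed. As written, the randomisation sections let people who enrol foresee the side of the next device, and the timeline does not prevent this. The size of any resulting bias cannot be estimated from the article. It depends on how often the two sides differ and on whether foreknowledge is used.

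The mismatch between 20 sets and mandatory replacement is internal to the article. At an assumed 5% to 10% loss, about 1 to 2 patients would enter without a specified allocation, and the chance of at least one is 64% to 88%. These figures rest on the assumed rates and on independent losses. The mismatch itself needs neither: a single dropout brings it about.

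**What to change.** Amend the three randomisation sections together, before the first patient enters:

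1. In Implementation {16c}, remove the principal investigator team from sequence generation. Name one existing sponsor staff member with no role in consent, screening, planning or surgery to generate and hold the list.
2. In Sequence generation {16a}, lengthen the list, for example to 30 sets. State that each replacement takes the next unused set and never that of a patient who left.
3. In Concealment mechanism {16b}, state that the next unused set is released only after consent, eligibility and the pre-operative CBCT have been recorded.

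The sample size, visits and procedures stay as they are. The cost is a longer list, a release step, and a short administrative delay before graft planning for each patient. If sets have already been seen by the enrolling team, their secrecy cannot be restored, so the change is worth most before recruitment begins.
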